### Secondary outcomes

2.9

The secondary outcome measures include weekly mean frequency of defecation, weekly mean stool appearance score, weekly mean stool urgency score, emotional state score, gut microbiome, and faecal metabolome.(1)Similarly, based on the diary (Appendix 2), the weekly mean frequency of defecation, the weekly mean stool appearance score, and the weekly mean stool urgency score within the past two weeks on day 0, day 14, day 28 to day 42 will be evaluated. It is noted that the weekly mean frequency of defecation, weekly mean stool appearance score, and the weekly mean stool urgency score on day 0 are obtained from the diary completed during screening period, Table 1.(2)The Depression, Anxiety and Stress Questionnaire (DASS-21) [38] (Appendix 3) will be completed online on day 0 (baseline), day 14, day 28, and day 42, and emotional state score calculated from DASS-21 will be used to assess the volunteers' emotional status, Table 1.(3)For the indicator of gut microbiome, DNA are extracted from stool sample using the QIAamp Fast DNA Stool Mini Kit (Qiagen, Hilden, Germany). An agarose gel electrophoresis and Nanodrop spectrophotometer are used to examine the quality of DNA. Then, shotgun metagenomic sequencing are performed for all samples using an Illumina HiSeq 2500 instrument. And sequence libraries are constructed by DNA fragments of ∼300 bp length which obtained from paired-end reads of ∼150 bp lengths generated by sequencing in bi-directions. In addition, the metagenomic analysis is performed from the following aspects: analysing alpha diversity and beta diversity in each group to determine the intra-groups differences in the microbiota compositions; analysing the inter- and intra-groups taxonomic characteristics at the levels of phylum, genus, and species to identify specific genes related to diarrhoea. Metagenomic biological pathway analysis are used to evaluate the effect of probiotics on the function of the gut metagenomics in patients with diarrhoea and hopefully to explore the metagenomic biological pathways contributing to the mechanism of probiotics on the treatment of diarrhoea.(4)For the indicator of faecal metabolome, briefly, stool samples treated by protein precipitation method and the supernatant are used for liquid chromatography tandem mass spectrometry (LC-MS/MS) analysis. The original data is subjected to peak alignment, retention time correction and peak area extraction through the XCMS-Plus program. The structure of metabolites is identified by accurate mass matching (<5 ppm) and two-level spectrum matching, and METLIN database is retrieved. After deleting the missing value > 50% and normalizing the data, multi-dimensional statistical analysis is performed, like unsupervised principal component analysis (PCA), supervised partial least squares discriminant analysis (PLS-DA) and potential difference metabolite analysis. Metabonomic analysis can further identify the potential differential metabolites of probiotics in treatment of diarrhoea and examine the correlation analysis between the gut microbiota and metabolites.

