### Statistical analysis

2.15

The following four datasets will be used for the analysis [1]: the data of all volunteers who completed the follow-up and [2] the data of three subgroups divided according to compliance (≥80%, 60–80%, and <60%), which will be analysed to validate the robustness of the analysis results. The following analysis methods will be used to analyse each dataset.

First, to analyse the inter-group differences in each outcome measure, Z test (as the sample size is quite more than 10, using Z test instead of Wilcoxon signed-rank sum test) will be used for the outcome measures, including the diarrhoea severity score, weekly mean frequency of defecation, weekly mean stool appearance score, weekly mean stool urgency score, and emotional state score, at each observation point. In the analyses, the *P*-value indicating statistical significance will be set at 0.05. More detailed information about how to analyse and present inter-group differences is clearly provided in Table 2.

**Table 2 tbl2:** The format to analyse and present the inter-group differences between probiotic and placebo groups at each observation point.

Groups	P5	P25	Median	P75	P95	Z value	*P*
*L. plantarum* p9							
Placebo							

Note: The data applied here includes the diarrhoea severity score, weekly mean frequency of defecation, weekly mean stool appearance score, weekly mean stool urgency score, and emotional state score; P5, P25, P75, P95 means the 5th, 25th, 75th, 95th percentile, respectively; Z = |T-n1*(N+1)/2–0.5|/SQRT [n1*n2(N+1)/12], n1 refers to the smaller sample size between the two compared groups, while n2 refers to the sample size of the other group; N = n1+n2; T is calculated using method of Wilcoxon signed-rank sum test.

Then, to identify the intra-group changing trends with the consecutive phases, namely, pre-, during and post-probiotic administrating, the *Kruskal-Wallis* rank sum test will be used for multiple comparisons of the diarrhoea severity score, weekly mean frequency of defecation, weekly mean stool appearance score, weekly mean stool urgency score, and emotional state score for each group, i.e., probiotic group or placebo group. In the analyses, the *P*-value indicating statistical significance will be adjusted to be 0.05/[k(k-1)/2], where k is the number of sample groups in the comparison. More detailed information about how to analyse and present inter-group differences is clearly provided in Table 3.

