**Table 3 tbl3:** The format to analyse and present the intra-group differences among the four observation points in a probiotic or placebo group.

Groups	P5	P25	Median	P75	P95	H value	*P*
Day 0							
Day 14							
Day 28							
Day 42							

Note: The data here includes the diarrhoea severity score, weekly mean frequency of defecation, weekly mean stool appearance score, weekly mean stool urgency score, and emotional state score; P5, P25, P75, P95 means the 5th, 25th, 75th, 95th percentile, respectively; H is calculated using method of *Kruskal-Wallis* rank sum test.

In addition, the statistical analyses of metagenomics and metabolomics will be performed using the R software (v.4.0.2) and Adobe Illustrator. PCA and PLS-DA analysis will be performed and visualized using the R package vegan, ggplot and ggpubr, and the adonis *P*-value will be generated based on 999 permutations. *t*-test, *Wilcoxon* test and *Kruskal-Wallis* test will be used to evaluate differences in various variables between and within groups; *P* values will be corrected for multiple testing using the Benjamini-Hochberg procedure. Meanwhile, Pearson and spearman correlations will be used to analyse the correlations between different indicators in clinical, metagenomics and metabolomics.

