Multidimensional outcomes are examined to produce a chain of evidence from causal improvements in metagenomic and metabolomic data to clinical symptoms and then to the emotional state. Chronic diarrhoea can disturb the patient's quality of life, work performance and wellbeing [10]; thereby, the relevant outcomes are chosen, including the diarrhoea severity score [33,34], weekly mean frequency of defecation, weekly mean stool appearance score [33,37], weekly mean stool urgency score [34], emotional state score [38] according to corresponding references [33,34,37,38]. The diarrhoea severity score is a comprehensive indicator calculated from weekly mean frequency of defecation, weekly mean stool appearance score, and weekly mean stool urgency score as described in “Primary outcome part”, so it is more reasonable to be the primary outcome than the left. Furthermore, both of inter- and intra-group differences will be analysed. In our opinion, the results of analysis are appropriate to present the effect of *L. plantarum* P9 on defecation and quality of life in individuals with chronic diarrhoea. Moreover, the study will try to explore the possible action modes of probiotics to improve chronic diarrhoea, from the aspects of gut microbiome and faecal metabolome. Gut microbiome has been found to be altered in chronic diarrhoea patients and may be a cause of chronic diarrhoea [12]. Probiotics are live organisms that when administered in adequate amounts confer health benefits to the host and improve the gut microbial balance [[13], [14], [15], [16], [17],^26^]. The detection of gut microbiome and faecal metabolome would provide an explanation for the efficacy of *L. plantarum* P9 on chronic diarrhoea. Thus, the set of multidimensional outcomes will form a chain of evidence.

A limitation is the way of follow up in this study (completing diary online daily), which may lead to bias about the effectiveness of probiotics. To overcome the limitation, a WeChat group is established for the cohort of volunteers, so the researcher can timely post messages via the WeChat group, keeping a good compliance; and an DMT is formed to promptly assess the study quality and safety. during the assessment, once an uncertainty about the data arises, the DMT can urge the data collectors to resolve it. The confounding factors are also prohibited. In such a way, the bias would be minimized as far as possible.

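### Four clinical secondary outcomes are tested between groups at three post-baseline visits, each at an unadjusted 0.05, with no order, key visit or exploratory label

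*Protocol article*

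**What the plan says.** Section 2.9 of the protocol article lists the outcomes: "The secondary outcome measures include weekly mean frequency of defecation, weekly mean stool appearance score, weekly mean stool urgency score, emotional state score", followed by the gut microbiome and the faecal metabolome. Table 1 schedules the four clinical ones at days 0, 14, 28 and 42. For the emotional state questionnaire, section 2.9 repeats this in words: it "will be completed online on day 0 (baseline), day 14, day 28, and day 42".

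Section 2.15 applies a rank-based Z test between groups to the primary score and to "weekly mean frequency of defecation, weekly mean stool appearance score, weekly mean stool urgency score, and emotional state score, at each observation point". The significance rule for these comparisons is "In the analyses, the *P*-value indicating statistical significance will be set at 0.05".

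The same section treats the other two families of tests differently:

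- Within-group comparisons between visits use 0.05 divided by the number of pairs.
- For the omics variables, "P* values will be corrected for multiple testing using the Benjamini-Hochberg procedure".

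Section 3 (Discussion) justifies each clinical outcome as relevant and describes the outcome set as a chain of evidence that ends at emotional state. It adds: "In our opinion, the results of analysis are appropriate to present the effect of *L. plantarum* P9 on defecation and quality of life" in people with chronic diarrhoea.

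**The concern.** The protocol is not silent on multiplicity. It sets three rules, and the randomised between-group clinical comparisons are the one family left at a plain 0.05. The within-group comparisons, which cannot show an effect against placebo, face a stricter threshold.

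As written, any of the 12 post-baseline secondary results below 0.05 may be called statistically significant. Nothing says which visit counts, whether one secondary ranks above another, or that the results are only supportive.

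Two features add weight. Emotional state lies wholly outside the primary score, so any statement on mood rests entirely on this uncorrected family. The other three secondaries come from the same diary items as the primary score, and the Discussion itself describes the primary as calculated from them, so they cannot independently confirm it. At stake is how far the trial report can go on stool form, urgency or mood.

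**Working it through.** **The plan's own figure.** The article states no error rate for the secondary family. Its one related figure is the sample size in section 2.13: difference 3, SD 6.8, α = 0.05, β = 0.20.

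n per group = 2 × (1.960 + 0.842)² × 6.8² / 3² = 80.7, rounded up to 81.

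This matches the stated 81. A one-sided 0.05 would give 64, so the plan's 0.05 is two-sided. The absolute value in the Table 2 statistic, "Z = |T-n1*(N+1)/2–0.5|/SQRT [n1*n2(N+1)/12", points the same way.

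**Inputs**

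- Clinical secondary outcomes: 4 (section 2.9).
- Post-baseline visits: 3, days 14, 28 and 42 (Table 1). Day 0 is left out because a difference there cannot be a treatment effect.
- Tests: 4 × 3 = 12.
- Level per test: 0.05 two-sided, so 0.025 in the direction favouring the probiotic.
- Correlations: not in the article. Assumed 0 to 0.7 between outcomes and 0 to 0.8 between visits.
- The compliance subgroups in section 2.15 are presented as robustness checks and are not counted.

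**Upper end: independent tests, all nulls true**

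- Any false difference, 12 tests: 1 − 0.95¹² = 0.460.
- False difference favouring the probiotic, 12 tests: 1 − 0.975¹² = 0.262.
- One visit, 4 tests: 1 − 0.95⁴ = 0.185, and 1 − 0.975⁴ = 0.096.

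**With correlation.** Test statistics were simulated as multivariate normal, with one common correlation between outcomes and one between visits, and at least 400,000 draws per setting. Any false difference counts |Z| > 1.96; a false benefit counts Z > 1.96 in the probiotic's favour only.

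| Between outcomes | Between visits | Any false difference | False benefit |
|---|---|---|---|
| 0 | 0 | 46% | 26% |
| 0.3 | 0.5 | 39% | 20% |
| 0.5 | 0.5 | 36% | 18% |
| 0.5 | 0.7 | 32% | 16% |
| 0.7 | 0.5 | 30% | 15% |
| 0.7 | 0.8 | 24% | 12% |

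For the four tests at one visit, with outcome correlation 0 to 0.7, the rates are 19% down to 13% in either direction and 10% down to 6.5% for a false benefit.

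As an extreme outside the assumed range, a correlation of 0.9 between all 12 statistics gives about 13% and 7%. These still exceed 5% and 2.5%.

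**Contrast within section 2.15.** With k = 4 visits, the within-group threshold is 0.05 / [4 × 3 / 2] = 0.05 / 6 = 0.0083. The between-group clinical threshold stays at 0.05.

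**After a change.** Bonferroni over 12 tests would use 0.05/12 = 0.0042 each; over four tests at one visit, 0.05/4 = 0.0125 each. Each holds the family at or below 5% (4.9% if the tests are independent). Holm, or a fixed order at 0.05 per step, over the four tests at one visit also holds 5%. An exploratory label leaves the rates as they are but removes the confirmatory reading.

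**The case against.** The strongest reply has four parts.

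1. **One primary outcome is named, and the trial is sized on it at day 28.** The Discussion also argues why it ranks above the others. This stands. A reader might infer that the plan has no hierarchy at all, or that the primary conclusion is inflated. Neither follows: secondary tests do not change the type I error of the day-28 primary. What is missing is an order, a key visit or a label within the secondary set.

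2. **The size depends on assumed correlations and on the event counted.** This also stands. A reader might infer roughly a 30% chance of a false secondary benefit. That figure is the either-direction rate under fairly strong assumed correlation and includes false harm. The benefit-only rate does not exceed about 26% for the 12 post-baseline tests, even if they are independent.

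3. **The Discussion sentence is an opinion about the whole analysis, primary included.** It is not a decision rule. This stands in part. No section says that a significant secondary would establish efficacy or rescue a failed primary, and that should not be read into the text. But the sentence places no limit on how secondary results may be used, and section 2.15 gives each a significance threshold.

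4. **Nominal secondary P values are common in academic trials, and ordering is often left to an analysis plan.** The corrections made elsewhere in section 2.15 do not commit the trial to controlling error across secondaries. It is fair that gatekeeping or Holm is a choice and not the correction of an error. But the 0.05 threshold at every visit is stated in section 2.15, so it is not a detail deferred to an unseen document. The range of possible claims can be narrowed by wording alone.

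**Conclusion.** The point holds as a limited one. Section 2.15 fixes an unadjusted 0.05 for 12 post-baseline between-group secondary tests, with no order, key visit or exploratory label, while it corrects the other two families.

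With all nulls true and the assumed correlations (0 to 0.7 between outcomes, 0 to 0.8 between visits), the chance of at least one false significant secondary difference is about 24% to 46% in either direction. It is about 12% to 26% for one favouring the probiotic, roughly 5 to 10 times the 2.5% of a single test. At one visit the rates are about 13% to 19% and 6.5% to 10%. These ranges rest on correlations the article does not give.

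The primary comparison at day 28 is untouched, so this bears on what may be claimed from the secondary outcomes and not on the main result. It should be settled before unblinding.

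**What to change.** In section 2.15:

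- Name day 28, the visit in the sample-size paragraph, as the only visit for any claim on the four clinical secondaries.
- State that secondary P values at the other visits are nominal and exploratory, with no significance claim.
- For the four day-28 secondaries, choose one of two routes. Either label them supportive only or, if the sponsor wants to claim on them, test them after a significant primary, by Holm at 0.05 or in a fixed order written down in advance.

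In the Discussion, limit the wording on efficacy to the outcomes that the chosen route allows.

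This costs wording only, with no new data or patients. The downside is that fewer secondary results can be called significant.

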### Primary outcome

2.8

The primary outcome is the diarrhoea severity score, which is set as to the gastrointestinal symptom rating scale (GSRS) [[33], [34], [35], [36]]. The outcome measure is equal to the sum of mean defecation frequency score per day, mean stool consistency score per time, and mean stool urgency score per time within the past 7 days (see Appendix 2). The diarrhoea severity score will be assessed on days 0 (baseline), 14, 28, and 42. A higher score indicates more severe diarrhoea, Table 1. The details of calculation are as follows.

A defecation diary developed with reference to the literatures [33,34,37] will be completed daily online by the volunteers (Appendix 2). Based on the diary, the mean defecation frequency score per day, mean stool consistency score per time, and mean stool urgency score per time will be obtained. The defecation frequency score is ranked as: 0-point, one to two a day; 1-point, three to four times a day; 2-point, five to six times a day; 3-point, seven times a day or more frequently. The mean defecation frequency score per day is equal to “total defecation frequency score within the past 7 days/7”. The stool appearance score refers to Bristol stool type (Appendix 1) and must be recorded for each defecation: types 4–7 correspond to 0–3 points, respectively. The mean stool consistency score per time is equal to “total stool consistency scores within the past 7 days/total times”. The stool urgency score must be also recorded for each defecation: 0-point, no urgency; 1-point, a little urgency; 2-point, sudden need to have a defecation that must be addressed immediately; or 3-point, incontinence resulting in uncontrolled defecation and may stain pants. The mean stool urgency score per time is equal to “total stool urgency score within the past 7 days/total times”.

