### Sample size

2.13

The trial obeys the principle of a superiority design. Combined pilot cases observation and experts’ opinion [35,36], it is estimated that the primary outcome, diarrhoea severity score on day 28, can differ by 3 points between the probiotics or placebo groups, with a standard deviation of 6.8. Given an *α* = 0.05 and a *β* = 0.20, the sample size is calculated to be at least 81 per group. After considering the drop-out rate (20% or lower), the sample size should be 97 or more per group. The final sample size is determined to be 100 per group with a total of 200 cases.

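### The analysis section tests the primary score between groups at every visit at an unadjusted 0.05 and does not say that day 28, named only in the sample-size paragraph, is the deciding test

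*Protocol article*

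**What the plan says.** Section 2.8 of the protocol article defines the primary outcome as the diarrhoea severity score and gives its schedule: "The diarrhoea severity score will be assessed on days 0 (baseline), 14, 28, and 42". Table 1 ticks the same four visits in the primary-outcome row. Neither place marks one visit as decisive.

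Section 2.13 does. It refers to "the primary outcome, diarrhoea severity score on day 28, can differ by 3 points between the probiotics or placebo groups" and derives 81 per group from that difference, an SD of 6.8, alpha 0.05 and beta 0.20.

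Section 2.15 sets out the between-group tests. They cover the primary score and four others, ending with "weekly mean stool urgency score, and emotional state score, at each observation point", and the P-value "indicating statistical significance will be set at 0.05". Table 3 counts four observation points, so day 0 is one of them. Section 2.15 also says "The following four datasets will be used for the analysis": all volunteers who completed follow-up, and three subgroups by compliance. It adds "The following analysis methods will be used to analyse each dataset". The purpose given for the subgroups is that they are data "which will be analysed to validate the robustness of the analysis results".

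The same section does correct for multiplicity elsewhere. The within-group comparisons use 0.05/[k(k-1)/2], and the metagenomic and metabolomic tests use the Benjamini-Hochberg procedure.

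**The concern.** The between-group comparison is the one that rests on randomisation and carries the efficacy claim. It is the one family of tests here for which a plain 0.05 is prescribed at every visit, while the within-group and omics tests are corrected. Since the article addresses multiplicity and fixes the level for each family, this is a stated rule and not a detail left to a separate analysis plan.

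The restriction to day 28 is made where the trial is sized and is not carried into the sections that define the outcome and its analysis. Someone working from 2.8, Table 1 and 2.15 could not tell which of three post-baseline p-values decides the trial. If the choice were made after the results are known, the 5% level used to size the trial would no longer describe the primary claim.

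The day-0 test is a separate, smaller fault. Under randomisation any difference before treatment is due to chance, so the test answers no useful question. It cannot support an efficacy claim either, so it is left out of the error rates below.

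**Working it through.** **Inputs**
- Difference 3, SD 6.8, alpha 0.05, beta 0.20, day 28: section 2.13.
- Unadjusted 0.05 for each between-group test: section 2.15.
- Post-baseline visits for the primary score: days 14, 28 and 42, so three tests (2.8, Table 1).
- Correlation of the test statistics between visits: not given. Assumed range 0 to 0.9.

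**Step 1. Reproduce the plan's sample size**

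n per group = 2 (z_alpha + z_beta)² SD² / difference²

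- Two-sided 0.05: 2 × (1.960 + 0.842)² × 6.8² / 3² = 80.65, rounded up to **81**. This matches the article.
- One-sided 0.05: 2 × (1.645 + 0.842)² × 6.8² / 3² = 63.5, rounded up to 64. This does not match.

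The sidedness is not stated, but 81 corresponds to one two-sided test at 0.05, at one visit.

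**Step 2. Error rate if day 28 alone decides**

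One test at 0.05 gives 5%.

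**Step 3. Error rate if any of the three post-baseline visits could decide**

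Independent tests: 1 − 0.95³ = 1 − 0.857 = 14.3%.

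Correlated tests: let Z14, Z28 and Z42 be standard normal under the null. The rate is 1 − P(all three |Z| < 1.96), obtained by numerical integration.
- Equal correlation r between all visits: 1 − ∫ φ(u) [Φ((1.96 − √r·u)/√(1−r)) − Φ((−1.96 − √r·u)/√(1−r))]³ du.
- Correlation that decays with time (AR(1): r between adjacent visits, r² between days 14 and 42): 1 − ∫ over |m| < 1.96 of φ(m) [Φ((1.96 − r·m)/√(1−r²)) − Φ((−1.96 − r·m)/√(1−r²))]² dm.

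| Assumed r | Equal correlation | AR(1) |
|---|---|---|
| 0 | 14.3% | 14.3% |
| 0.5 | 12.5% | 12.9% |
| 0.7 | 10.9% | 11.4% |
| 0.8 | 9.8% | 10.3% |
| 0.9 | 8.4% | 8.8% |

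The range is about 8% to 14%. The rate crosses 10%, twice the nominal level, at a correlation of roughly 0.8.

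**Step 4. Compare the two ways to restore 5%**
- Name day 28 as the single primary test: n stays at 81 per group.
- Split alpha over the three visits by Bonferroni, 0.05/3 = 0.0167 each: 2 × (2.394 + 0.842)² × 6.8² / 3² = 107.6, rounded up to 108 evaluable per group. That exceeds the 100 per group planned before drop-out.

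**The case against.** The strongest reply is that the article does name a primary visit. Section 2.13 equates the primary outcome with the score on day 28, and a list of assessment days or a visit schedule is not a list of co-primary endpoints. On that reading the primary error rate among completers is 5%. The point has force. No sentence in the article says that significance at any visit, or in any dataset, counts as success.

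A reader might therefore go too far in three ways.

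- *The false-positive rate is more than doubled.* This needs an any-visit rule that the article does not state. Even under such a rule it fails once the between-visit correlation reaches about 0.8 to 0.9, and the article gives no correlation.
- *The four datasets multiply the primary error.* Under assumed compliance splits (80/15/5, 90/7/3 or equal thirds), simulation gives about 15% to 16% for day 28 in any of the four datasets, and about 25% to 41% for any of the three visits in any dataset. But 2.15 calls the compliance subgroups robustness checks, so these figures do not describe its stated purpose.
- *All five clinical scores, or the day-0 test, belong in the primary error rate.* Four of the scores are labelled secondary, and a pre-treatment comparison cannot yield an efficacy claim.

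It may also be said that a hierarchy for secondary outcomes belongs in an analysis plan that is not shown. That is fair for the secondary scores. It does not cover the primary score, for which 2.15 itself prescribes the tests and the level. What survives is that 2.8 and 2.15 do not carry over the day-28 restriction on which the sample size depends.

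**Conclusion.** The point holds as an inconsistency that should be corrected. Section 2.13 sizes the trial for one test at day 28, while 2.15 specifies three post-baseline tests of the primary score at 0.05 each and ranks none of them. The primary error rate is 5% if only day 28 in completers counts, and about 8% to 14% if a result at any post-baseline visit in completers could be claimed. The second range rests on normal test statistics and an assumed correlation of 0.9 down to 0. Which rate applies cannot be settled from 2.8 and 2.15 as written; only 2.13 points to the first. The day-0 significance test serves no purpose but does not affect these rates.

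**What to change.** - State in 2.8 and again in 2.15 that the between-group comparison of the diarrhoea severity score on day 28, in one named dataset, is the single primary test at two-sided 0.05, in line with 2.13.
- Make days 14 and 42 and the four other scores secondary, and either adjust them (for example by Holm) or label them as not confirmatory.
- Drop the significance test at day 0 and describe baseline by group instead.
- State that the compliance subgroups, already described as robustness checks, cannot carry the primary claim.

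These are changes of wording. They restore the level behind the 81 per group and leave that number unchanged. The cost is that a difference at day 14 or day 42 can no longer support a primary claim. The article reports 174 enrolled with recruitment still open, so the change could be made before the final unblinding.

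Replacing completers with all randomised volunteers as the named dataset would be a separate change. It needs a method for missing data and is not part of this fix.

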	Gut microbiome		**✓**		**✓**	**✓**
	Faecal metabolome		**✓**		**✓**	**✓**
Safety measures	Adverse events (AEs)			**✓**	**✓**	**✓**
	Serious adverse events (SAEs)			**✓**	**✓**	**✓**
Verification of compliance with the intervention					**✓**	
Special situations related to defecation (e.g., concomitant medications)			**✓**	**✓**	**✓**	**✓**

Note: The outcome measures, weekly mean frequency of defecation, weekly mean stool appearance score and weekly mean stool urgency score are calculated from the defecation diary. The defecation diary completed from day −14 to −1 will be used for volunteer selection and baseline data. The detection of gut microbiome will be conducted within 2 months after the end of follow-ups, and the detection of faecal metabolome will be implemented within 2 months when data analysis finds that the probiotics present significant effect on gut microbiome.

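### The within-arm tests apply Kruskal-Wallis, which needs independent groups, to the same volunteers on days 0, 14, 28 and 42, so the intra-group p-values are invalid (conservative if scores correlate positively within person)

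*Protocol article*

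**What the plan says.** Section 2.15 of the protocol article gives the intra-group analysis its own purpose: "to identify the intra-group changing trends with the consecutive phases, namely, pre-, during and post-probiotic administrating". The method is Kruskal-Wallis, run separately in the probiotic and placebo arms: "rank sum test will be used for multiple comparisons of the diarrhoea severity score", together with weekly defecation frequency, stool appearance, stool urgency and the emotional state score.

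Table 3 is titled "The format to analyse and present the intra-group differences among the four observation points in a probiotic or placebo group". Its rows are days 0, 14, 28 and 42, and its note says "H is calculated using method of" Kruskal-Wallis. The significance level is 0.05/[k(k−1)/2], where k is the number of groups compared.

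Two other statements show that the rows are not separate people. Section 2.8: "The diarrhoea severity score will be assessed on days 0 (baseline), 14, 28, and 42". Section 2.15, on the main dataset: "the data of all volunteers who completed the follow-up".

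On use of the results, the Discussion says "both of inter- and intra-group differences will be analysed" and treats the analyses together as showing the product's effect. The note to Table 1 says that the diary from days −14 to −1 "will be used for volunteer selection and baseline data".

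**The concern.** Kruskal-Wallis compares k independent samples. Here the k samples are repeated scores on one set of completers. The test pools all scores, ranks them, and treats stable differences between volunteers as random error, so its reference distribution is wrong. No paired or repeated-measures method is named for these five outcomes, one of which is the primary score. This is a stated choice rather than a detail left to an analysis plan: the article fixes the test, the statistic, the threshold and the table layout.

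The threshold adds a second difficulty. Dividing 0.05 by the number of pairs is a correction for pairwise tests, but the only statistic named is the overall H. Read literally, a single overall test is judged at 0.0083.

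At stake are the intra-group p-values in both arms and in all four datasets (completers and three compliance subgroups), and the weight a reader gives them beside the between-group result.

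**Working it through.** **1. Are the samples independent?** No. Section 2.8 schedules each volunteer for all four days, and section 2.15 analyses those who completed follow-up. Each volunteer should therefore appear in every row of Table 3.

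**2. Threshold.** With k = 4 there are 4 × 3/2 = 6 pairs, and 0.05/6 = 0.0083. This is the Bonferroni level for six pairwise tests.

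**3. Sample size, to fix the scope.** Inputs from section 2.13: difference 3, SD 6.8, α 0.05 (two-sided assumed), power 0.80. n = 2 × [6.8 × (1.960 + 0.842)/3]² = 80.65, so 81 per group. The plan's figure reproduces. It belongs to the between-group day-28 comparison and does not depend on Kruskal-Wallis.

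**4. Direction and size of the error.** The article gives no within-person correlation ρ, so 0.3 to 0.7 is assumed, equal between all visits. With no change over time, H then behaves approximately as (1 − ρ) times a chi-square on 3 df, with ρ the rank correlation. The 5% critical value is 7.815, so the true error is about P(χ²₃ > 7.815/(1 − ρ)):
- ρ = 0.3: 7.815/0.7 = 11.16, giving 1.1%
- ρ = 0.5: 7.815/0.5 = 15.63, giving 0.13%
- ρ = 0.7: 7.815/0.3 = 26.05, giving about 0.001%

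Simulation (81 volunteers, four visits, normal scores, 5,000 runs per setting) agrees: 5.0% at ρ = 0, 1.3% at 0.3, 0.2% at 0.5 and 0.0% at 0.7. Friedman stays between 4.7% and 5.4%.

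**5. Power.** The article gives no expected change over time, so a range is shown. d is the largest mean fall in SD units. Pattern A is a sustained fall (0, −d/2, −d, −d; n = 80). Pattern B returns halfway by day 42 (0, −d/2, −d, −d/2; n = 81). Entries are Kruskal-Wallis / Friedman power in %; simulation error is a few points at most.

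| d | ρ | A at 0.05 | B at 0.05 | B at 0.0083 |
|---|---|---|---|---|
| 0.30 | 0.3 | 34 / 47 | 23 / 35 | 7 / 14 |
| 0.30 | 0.5 | 27 / 60 | 17 / 47 | 3 / 23 |
| 0.30 | 0.7 | 21 / 86 | 9 / 72 | 1 / 45 |
| 0.44 | 0.3 | 78 / 84 | 59 / 69 | 30 / 43 |
| 0.44 | 0.5 | 77 / 94 | 55 / 83 | 22 / 59 |
| 0.44 | 0.7 | 80 / 99 | 53 / 97 | 15 / 89 |
| 0.67 | 0.3 | >99 / >99 | 97 / 97 | 84 / 89 |
| 0.67 | 0.5 | >99 / >99 | 98 / >99 | 86 / 97 |
| 0.67 | 0.7 | >99 / >99 | 99 / 100 | 90 / 100 |

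At d = 1.0 (pattern B) both tests are at about 100% at either level.

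**6. Which row applies?** 0.44 is 3/6.8, the plan's between-group figure, used here only as a reference point. As defined in section 2.8, the score is a sum of three means each scored 0 to 3, so it runs from 0 to 9 and its SD cannot exceed about 4.5. On that scale a 3-point change is at least 3/4.5 = 0.67 SD, where the loss is small. The documents do not say whether the within-arm change will be larger or smaller than 3 points.

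**The case against.** The strongest defence is that this is a supporting analysis. Efficacy has its own between-group test and Table 2, the sample size rests on that comparison, and under positive correlation the error here is conservative, so it does not create false positives. All of this stands. It limits the severity but does not make the test valid.

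A reader might infer that most of the power to see change is lost. The documents do not support that as a general statement, because they give neither the correlation nor the expected change. It is true for small changes with high correlation and untrue for low correlation or larger changes.

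A reader might also infer that regression to the mean by itself will produce improvement in both arms. That is too strong. The screening diary is used for selection, but no severity cut-off on it is stated, so regression is plausible and its size unknown. It is also a separate matter that changing the test would not cure.

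On the threshold, the text speaks of multiple comparisons and Table 3 is an empty layout, so pairwise testing may be intended. That is fair, but no pairwise test is named.

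On the microbiome and metabolome, section 2.15 lists t, Wilcoxon and Kruskal-Wallis tests for differences between and within groups. It does not say that the t and Wilcoxon tests are unpaired, so only within-group use of Kruskal-Wallis can be criticised.

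Finally, the article nowhere says it will infer efficacy from significance in one arm and not the other. The request to label intra-group results descriptive rests on the Discussion, which counts them toward the product's effect.

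**Conclusion.** Wrong as written, and should be fixed. The mismatch between the test and the repeated-measures data follows from the article's text and needs no assumption. That the p-values are conservative rests on positive within-person correlation, which is to be expected when a chronic symptom is scored repeatedly in the same people. The error rates in the working rest on correlations of 0.3 to 0.7, and the power figures also on an assumed size and pattern of change. All of them assume normal scores with equal correlation and no ties or missing values, whereas the real scores are bounded and may tie. The power loss runs from substantial at 0.3 SD to almost none at 0.67 SD or more when tested at 0.05. If 0.0083 is applied to the overall H, some loss remains at 0.67 SD (84–90% against 89–100% in pattern B). The between-group comparison of the primary outcome and the 81 per group are not touched by this defect.

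**What to change.** In section 2.15 and Table 3:

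- Replace Kruskal-Wallis with the Friedman test, or a mixed model with visit as a repeated factor, at 0.05 for the overall within-arm comparison.
- Follow with paired Wilcoxon signed-rank tests for the six pairs of visits at 0.0083, and give Table 3 the matching statistic and pairwise p-values.
- State that intra-group results are descriptive and that efficacy is concluded only from the between-group comparison. Give the reason: day-0 values of the four diary-based outcomes come from the screening diary used for selection, so regression to the mean may contribute to within-arm change.
- For within-group microbiome and metabolome comparisons, name paired or repeated-measures forms in place of Kruskal-Wallis.

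The cost is revised wording, a changed table layout and a few lines of code. No new data or volunteers are needed.
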